**Methods and analyzes::**

A randomized, triple-blind, placebo-controlled clinical trial will be carried out. Healthy male volunteers will be randomly distributed into 4 experimental groups: PBMT before and after training sessions + PBMT during detraining, PBMT before and after training sessions + placebo during detraining, placebo before and after training sessions + PBMT during detraining, and placebo before and after training sessions + placebo during detraining. The aerobic endurance training sessions will be carried out using motorized treadmills during 12 weeks, and the detraining period will consist in the next 4 weeks after that. It will be analyzed the time until exhaustion, maximal oxygen uptake (VO_2max_), and fat percentage of volunteers.

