### Randomization and blinding and experimental groups

2.4

To avoid selection bias and to ensure that all individuals are randomly allocated to any group, balanced block randomization will be performed based on the primary outcome (time to exhaustion in the progressive treadmill test) by a researcher who will have no contact with the study subjects or the other researchers involved in the project.

A researcher will program the device (PMBT or placebo) and will be instructed not to inform the volunteers or other researchers as to the type of treatment (PMBT or placebo). Therefore, the researcher responsible for the treatment will be blinded to the type of treatment being administered to the volunteers. The sounds and signals emitted from the device as well as the information displayed on the screen will be identical, regardless of the type of treatment (PMBT or placebo).

Randomization labels will be created through the random.org website, and a series of sealed, opaque, and numbered envelopes will be used to ensure confidentiality and will determine to which experimental group each volunteer will be allocated. Volunteers will be allocated as described below:

**A**: PBMT before and after the aerobic training sessions (12 weeks, 3 times a week) and PBMT during the detraining period (4 weeks, 3 times a week).**B:** PBMT before and after the aerobic training sessions (12 weeks, 3 times a week) and placebo during the detraining period (4 weeks, 3 times a week).**C:** Placebo before and after the aerobic training sessions (12 weeks, 3 times a week) and PBMT during the detraining period (4 weeks, 3 times a week).**D:** Placebo before and after the aerobic training sessions (12 weeks, 3 times a week) and placebo during the detraining period (4 weeks, 3 times a week).

The individuals randomly allocated to the different groups will be subjected to 12 consecutive weeks of aerobic endurance training in a motorized treadmill, with 3 training sessions per week on nonconsecutive days.

After the 12-week training period, the volunteers will receive the treatment, either PBMT or placebo, depending on the group to which they were allocated, during 4 weeks (3 times a week) without training.

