The evaluations described below will be performed before starting the protocol (baseline) and after 4, 8, and 12 weeks of aerobic endurance training, as well as after 4 weeks without training (detraining period) at 16th week. A flowchart summarizing the procedures of this study is presented in Fig. 1.

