### Statistical analysis

2.6

The primary outcome will be time until exhaustion obtained from progressive treadmill test. The secondary outcomes are VO_2max_ and fat percentage test. The intention-to-treat analysis will be followed a priori. All the data will be analyzed by a blinder researcher not involved in data collection. The findings will be tested for their normality using the Shapiro–Wilk test. Parametric data will be expressed as mean and standard deviation and nonparametric data as median and respective upper and lower limits. Parametric data will be analyzed by 2-way repeated measures analysis of variance (ANOVA; time vs experimental group) with post-hoc Bonferroni correction. Nonparametric data will be analyzed using the Friedman test and, secondarily, the Wilcoxon signed-rank test. Data will be analyzed in terms of both their absolute values and their percentage of change based on the values established in the baseline. The significance level will be set at *P* < .05.

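### If normality is rejected, the named fallback tests (Friedman, then Wilcoxon signed-rank) compare only visits within men, so that branch has no test of PBMT against placebo

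*Protocol article*

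**What the plan says.** The design has parallel groups: "Healthy male volunteers will be randomly distributed into 4 experimental groups" (Abstract). Sealed envelopes "will determine to which experimental group each volunteer will be allocated" (section 2.4), so each man belongs to one group throughout. He is measured at baseline and "after 4, 8, and 12 weeks of aerobic endurance training, as well as after 4 weeks without training (detraining period) at 16th week" (section 2.4), which makes five visits.

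Section 2.6 then sets the analysis:

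- Outcome: "The primary outcome will be time until exhaustion obtained from progressive treadmill test".
- Switch: "The findings will be tested for their normality using the Shapiro–Wilk test".
- If normal: "Parametric data will be analyzed by 2-way repeated measures analysis of variance (ANOVA; time vs experimental group) with post-hoc Bonferroni correction".
- If not normal: "Nonparametric data will be analyzed using the Friedman test and, secondarily, the Wilcoxon signed-rank test".
- Scale: "Data will be analyzed in terms of both their absolute values and their percentage of change based on the values established in the baseline".

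No Kruskal–Wallis, Mann–Whitney, rank-based analysis of covariance or other between-group rank method is named anywhere in the article.

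**The concern.** The Friedman test and the Wilcoxon signed-rank test need observations that are linked in blocks or pairs. In this trial the only linked observations are the visits of the same man. The tests can therefore show that time to exhaustion changes over the weeks. They cannot show that it changes differently under PBMT and placebo.

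The aim of the trial is the effect of PBMT during detraining, and the sample size in section 2.2 rests on PBMT against placebo. On the nonparametric branch that question has no test. The outcome data themselves, through the normality test, decide whether the primary outcome gets one.

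A report confined to this branch could then speak about treatment only by setting within-arm results side by side: a significant loss in a placebo arm, a non-significant loss in a PBMT arm. That is not a test of the difference between arms, and its error rate is not controlled at 5%.

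**Working it through.** The plan gives no figure for this branch, so there is none to reproduce. The check has four steps.

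**Step 1. What each branch can compare.**

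| Branch | Method named | Compares visits | Compares groups |
|---|---|---|---|
| Normal | 2-way repeated measures ANOVA | yes | yes |
| Not normal | Friedman | yes | no |
| Not normal | Wilcoxon signed-rank | yes (two at a time) | no |

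The Friedman test ranks values within each man, so a constant added to all of a man's values drops out. As a check on simulated data (15 men, 5 visits), 76.78 s was added to every value of one arm. This is the pilot difference, 923.60 − 846.82. The arm's Friedman statistic was 1.653 before and 1.653 after.

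**Step 2. What the tests respond to.** A simulation of four arms of 15 men over five visits was run 1,500 times per scenario. The assumptions were skewed errors and mean times of 700, 770, 830, 880 and 846.82 s, with any PBMT effect added at week 16.

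| Test | Rejects, no PBMT effect | Rejects, 76.78 s effect |
|---|---|---|
| Friedman, all men pooled | 100% | 100% |
| Kruskal–Wallis on week-12-to-16 change, 4 arms | 6.1% | 92% |
| Mann–Whitney on the same change, C against D | 5.8% | 76.7% |

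The Friedman test detects the course of training and gives the same answer with or without a treatment effect. With no effect, the signed-rank test of week 12 against week 16 rejected in about 40% of runs in each of arms C and D, because both arms truly lose 880 − 846.82 = 33.18 s. The two between-group tests answer the question.

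**Step 3. How often the fallback would be used.** Section 2.6 does not say how Shapiro–Wilk is applied. For truly normal data at the 5% level:

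- One test on group-centred values: about 5%.
- A test in each of 4 × 5 = 20 cells, with any failure triggering the switch: 1 − 0.95^20 = 64% if the cells were independent. Simulation with 15 per cell gave about 63% at visit correlation 0, 59–62% at 0.7 and 50–52% at 0.9.

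**Step 4. The false pattern, if arms are judged by within-arm significance.** Assumptions:

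- SD 84 s, from the pilot: √((65.77² + 99.23²)/2) = 84.18.
- Visit correlation 0.7, which is not in the article.
- 15 men per group (section 2.2).
- The same true loss from week 12 to week 16 in every arm.

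The SD of a man's change is 84 × √(2 × (1 − 0.7)) = 65.1 s. Let p be the chance that the signed-rank test is significant in one arm. The false pattern in one pair (placebo significant, PBMT not) has probability p(1 − p), which cannot exceed 25%. In at least one of the two pairs (A/B or C/D) it has probability 1 − (1 − p(1 − p))².

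| True loss | p (simulated) | One pair, p(1 − p) | Either pair |
|---|---|---|---|
| 30 s | 0.366 | 0.232 | 0.41 |
| 45 s | 0.680 | 0.218 | 0.39 |
| 60 s | 0.900 | 0.090 | 0.17 |
| 80 s | 0.990 | 0.010 | 0.02 |

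Repeated simulations agree within a few percentage points: 30 s gave 24–25% for one pair and 41–44% for either, and 80 s gave 0.6–1% and 1–2%.

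**The case against.** **The default branch is sound on this point.** It is: the repeated measures ANOVA has a group factor. A reader might infer that the trial has no between-group test at all. The article does not support that; the gap exists only if normality is rejected.

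**The trigger may be rare.** This also stands in part. A reader might infer that the fallback is more likely than not to be used, from the 64% above. That needs a rule of 20 separate tests with one failure switching the outcome, and the article states no such rule. With one test on normal data the rate is about 5%.

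**Nobody says arms will be judged by within-arm significance.** Correct. Section 2.6 does not say whether Friedman is run by arm or pooled, or how a conclusion would be drawn. Step 4 shows what would follow from that practice; it does not describe a planned one. A reader might also take 42% as the error rate of a single comparison. It is not: it counts either of two pairs, and one pair cannot exceed 25%. At a loss of 80 s both rates fall to about 1–2%.

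**Randomisation blocks could serve as Friedman blocks.** Section 2.4 mentions balanced blocks based on the primary outcome, but nothing describes matched sets of men analysed together. This does not rescue the test.

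**Percentage change might supply the comparison.** It alters the scale, not the test.

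**The full analysis plan may supply it.** The point is not an omission. The article names specific tests, and they do not fit the design.

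**Conclusion.** The point stands as a conditional defect. On the nonparametric branch the plan names only related-samples tests, so the randomised comparison is untested there for every outcome, including the primary one. This follows from the structure of the tests and needs no numerical assumption.

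Its size does need assumptions. For truly normal data the branch would be entered in about 5% of trials under a single normality test, and in roughly 50–65% under a rule of any failure among 20 cells. If within-arm significance were then compared, a false finding in favour of PBMT would arise in about 1–25% of trials for one pair of arms, or about 1–42% for either of two pairs, for losses of 80 s down to 30 s common to all arms. The loss sizes and the visit correlation of 0.7 are assumed; the SD of 84 s comes from a pilot with 5 men per group.

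**What to change.** **Required.** In section 2.6, replace the Friedman and Wilcoxon signed-rank tests with a method that compares groups on the change from week 12 to week 16. Suitable choices are a rank-sum test stratified by training treatment (van Elteren), rank analysis of covariance, or a permutation test. This alone restores a treatment comparison on the nonparametric branch.

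**Preferred.** Remove the Shapiro–Wilk switch. Keep one model-based between-group analysis as primary whatever a normality test shows, check its residuals, and use the rank or permutation test as a sensitivity analysis. This also cures a separate weakness, the choice of the primary test by the outcome data.

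**Cost.** Wording in the protocol and the analysis plan only. No change to recruitment, visits or measurements.

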Various clinical training methods and protocols for performance enhancement, health promotion, and rehabilitation are used by different groups, including athletes, physically active individuals, sedentary individuals, and patients with different disorders and diseases. Among the training types and protocols, aerobic endurance training stands out. However, training protocols very often require discontinuation due to illness, injury, or other factors that may alter the capacity for physical activity, thereby causing a rapid loss of aerobic endurance conditioning,^[21]^ which represents a challenging problem in clinical practice. It should also be noted that, thus far, no evidence or consensus on any particular resource or method that may decrease the effects of detraining has been found.

An interesting study conducted by Wasik et al^[22]^ assessed the effects of PBMT on the oxidative metabolism of peripheral blood cells (erythrocytes, granulocytes, and lymphocytes) by irradiating heparinized blood samples from 15 volunteers. After irradiation, partial pressure of oxygen (PO_2_) and oxygen saturation (SaO_2_) increased, which shows that PBMT-induced photochemical reactions in blood cells may enhance the oxygen-carrying ability of blood. These interesting findings suggest that PBMT may attenuate the loss of performance observed during the detraining period after an aerobic endurance training program because oxygen transport and, consequently, the ability of muscles to use it, decrease during the detraining period.

Therefore, the effects of PBMT on aerobic endurance detraining remain unknown and it is a scientific challenge that will represent a key advance in the knowledge of this field when it is overcome. With this aspect in mind, this project aims to assess the ergogenic effects of PBMT during the detraining period after completing an aerobic endurance training protocol.

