### Subjects and sample size

2.2

As no studies assessing the effects of PBMT during the detraining period after an aerobic training program are currently available, the number of participants per group in the present study was calculated based on a pilot study, with 5 volunteers per group, which was conducted by our research group in order to estimate the sample size. A β value of 20% and an α of 5% were used to calculate the sample size.

The pilot study showed that applying PBMT during the detraining period resulted in a time to exhaustion (primary outcome of this study) of 923.60 seconds (65.77 standard deviation) during the progressive treadmill test, whereas applying the placebo during the detraining period resulted in a time to exhaustion of 846.82 seconds (99.23 standard deviation). We used the Researcher's Toolkit to calculate the sample (https://www.dssresearch.com/KnowledgeCenter/toolkitcalculators/samplesizecalculators.aspx).

On the basis of the aforementioned parameters used to calculate the sample, we found 15 volunteers per group, for a total of 60 volunteers. Therefore, predicting a 20% sample loss, 72 healthy, physically inactive male volunteers aged from 18 to 35 years will be recruited for the study to ensure a final sample size of 60 volunteers. As the PBMT device used in the study causes no harmful thermal effects,^[23]^ volunteers of different skin colors will be recruited.

Volunteers will be informed about all study procedures and will be asked to sign the Informed Consent Form before their enrollment in the study.

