#### Photobiomodulation therapy (PBMT)

2.2.4

PBMT or placebo will be applied before and after each training session. This irradiation protocol was tested and optimized in a previous study conducted by our research group.^[17]^ The results of this study^[17]^ showed that PBMT before and after each training session was the most effective in enhancing the effects of aerobic training. PBMT will be applied bilaterally using the direct contact method with light pressure on the skin at different sites, namely 9 sites on the knee extensor muscles (Fig. 2A), 6 sites on the knee flexor muscles, and 2 sites on the plantar flexor muscles (Fig. 2B).

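### The aim concerns weeks 12 to 16, but the only stated change score starts at week 0 and week 12 serves as neither reference nor covariate

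*Protocol article*

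**What the plan says.** The Introduction sets the aim: "this project aims to assess the ergogenic effects of PBMT during the detraining period after completing an aerobic endurance training protocol". The Discussion likewise speaks of keeping the gains from training.

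Section 2.4 defines four arms. A and B receive PBMT in training, and C and D receive placebo. In detraining, A and C receive PBMT, and B and D receive placebo. The visit schedule follows: "The evaluations described below will be performed before starting the protocol (baseline) and after 4, 8, and 12 weeks of aerobic endurance training", with a last visit at week 16 after four weeks without training. Baseline is thus week 0, and only the week-16 visit comes after the detraining treatment.

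Section 2.6 gives a two-way repeated-measures ANOVA (time by group) with Bonferroni post-hoc tests. It adds: "Data will be analyzed in terms of both their absolute values and their percentage of change based on the values established in the baseline". It names no primary visit, group pair or scale, and no week 12-16 contrast.

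The PBMT section reports from the group's earlier study that "PBMT before and after each training session was the most effective in enhancing the effects of aerobic training". The authors therefore expect a training-phase benefit, but they give no size for it.

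**The concern.** Retention of fitness is week 16 judged against week 12. The protocol does more than leave this open: it fixes a reference visit, and that visit precedes both treatment phases.

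On the protocol's own expectation, A and B enter detraining fitter than C and D. Week-16 values in seconds, or as percentage change from week 0, still contain that lead. Two consequences follow.

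- The group-by-time interaction can be significant because of training-phase PBMT alone, so it cannot by itself answer the question asked.
- A-C and B-D differ only in training treatment. A-D differs in both phases with both effects pointing the same way, and B-C differs in both with the effects opposed. None of the four isolates detraining PBMT.

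Without a named contrast, the published conclusion can turn on which pair and scale is reported. Even the clean pairs, A-B and C-D, give up the precision that the measured week-12 value would add.

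**Working it through.** **Inputs.** Section 2.2 gives pilot times to exhaustion of 923.60 s (SD 65.77) with PBMT and 846.82 s (SD 99.23) with placebo, 15 per group, α 5% and power 80%. It does not state whether the test is one- or two-sided.

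- Difference: 923.60 − 846.82 = 76.78 s.
- Pooled SD: √((65.77² + 99.23²)/2) = 84.18 s.

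**The plan's own figure.** n = 2 × 84.18² × (z_α + z_β)² / 76.78². This gives 14.86, so 15 per group, one-sided, and 18.87, so 19, two-sided. The stated 15 is reproduced one-sided. The calculation uses a level of time to exhaustion, not a loss since week 12. Everything below is two-sided.

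**What each pair carries at week 16.** Suppose training PBMT adds G seconds, all of it is kept, and detraining PBMT does nothing. G and full retention are assumptions.

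| Contrast | Week 16, seconds or change from week 0 in seconds | Week 12-16 change |
|---|---|---|
| A − B | 0 | 0 |
| C − D | 0 | 0 |
| A − C, A − D, B − C, B − D | G | 0 |

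**How often A versus D is significant with no detraining effect.** SE = 84.18 × √(2/15) = 30.74 s. Noncentral t, 56 df; critical value 2.003 at 5%, and 2.735 at 0.05/6 for the six pairs of four groups.

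| Assumed G | G / SE | Uncorrected | Bonferroni, six pairs |
|---|---|---|---|
| 40 s | 1.301 | 25% | 8% |
| 76.78 s | 2.498 | 69% | 41% |

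The second row only borrows the size of the planning difference as an upper illustration.

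**The omnibus interaction in the same setting.** Let G = 40 s build up linearly to week 12 and then hold, so the fractions of G at the five visits are 0, 1/3, 2/3, 1, 1 (mean 0.6). Their squared deviations sum to 0.7556. Under compound symmetry with between-visit correlation r, the noncentrality is 15 × 40² × 0.7556 / (84.18² × (1 − r)). With 12 and 224 df:

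| Assumed r | Noncentrality | Interaction significant |
|---|---|---|
| 0.5 | 5.1 | 24% |
| 0.7 | 8.5 | 41% |
| 0.8 | 12.8 | 61% |
| 0.9 | 25.6 | 94% |

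**The percentage scale.** The same 10% loss after week 12 reads as 1.20 × 0.90 − 1 = +8% from week 0 after an assumed 20% training gain, and as 1.30 × 0.90 − 1 = +17% after an assumed 30% gain.

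**Precision from week 12.** Adjustment multiplies the variance by 1 − r², where r is now the week 12-16 correlation. The documents do not give it, so a range is assumed. The effect is 76.78 s, with 56 df throughout; the one df spent on the covariate does not change the rounded figures.

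| r | Variance factor | SE, 15 v 15 | Power, 15 v 15 | SE, 30 v 30 | Power, 30 v 30 |
|---|---|---|---|---|---|
| unadjusted | 1 | 30.74 | 69% | 21.73 | 93% |
| 0.5 | 0.75 | 26.62 | 81% | 18.82 | 98% |
| 0.7 | 0.51 | 21.95 | 93% | 15.52 | >99% |
| 0.8 | 0.36 | 18.44 | 98% | 13.04 | >99% |
| 0.9 | 0.19 | 13.40 | >99% | 9.47 | >99% |

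The 30 v 30 columns pool A with C and B with D. The step from 69% to 93% comes from pooling; only the movement down each column comes from week 12. A plain change score has variance factor 2(1 − r), which is 1 at r = 0.5, so it gains nothing there. Covariate adjustment is the better choice.

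**The case against.** Three points weigh on the other side.

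First, a reader might infer that every outcome is referenced to week 0. Section 2.6 does not say that: absolute values are analysed too, and the ANOVA has weeks 12 and 16 among its levels, so a post-hoc 12-versus-16 test is possible. This stands. What remains is that no such test is named, and the only stated change score starts at week 0.

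Second, a reader might infer that the detraining effect is confounded across the trial. It is not. A and B share training treatment, as do C and D, so randomisation makes their week-16 comparisons unbiased in expectation on either scale. For these pairs the loss is precision only.

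Third, a reader might infer that A versus D is the protocol's detraining test. Nothing in the article says so, and a difference there would be a correct result for the combined regimen. The sample-size section points towards PBMT versus placebo during detraining. The 25% is therefore the chance of a result open to misreading, not a type I error rate of a planned test.

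It can also be said that covariates and the ranking of scales are commonly left to an analysis plan. That is fair as to detail, but here the article itself fixes a model and a reference visit that do not match its aim.

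**Conclusion.** The point holds in limited form. The protocol does not name the contrast that answers its aim, its one stated change score starts before training, and the measured week-12 value goes unused. The omnibus interaction and the four pairs that differ in training treatment carry any training-phase gain; A-B and C-D do not.

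The 25% and 8% for A versus D rest on an assumed 40 s gain, fully retained, no detraining effect, SD 84 s and 15 per arm. The interaction figures also assume linear build-up and compound symmetry. The variance reduction of 25% to 81% rests on assumed correlations of 0.5 to 0.9. The power figures further assume that the pilot difference of 76.8 s carries over after week-12 adjustment, which requires pilot groups that were alike at week 12. The pooled figures assume that the detraining effect does not depend on training allocation.

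This should be fixed, but it does not invalidate the design, because the randomised arms already contain unbiased detraining comparisons.

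**What to change.** In section 2.6, or in an analysis plan completed before unblinding:

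1. Name one primary analysis: week-16 time to exhaustion in seconds, PBMT versus placebo during detraining, adjusted for week-12 time to exhaustion and training-phase allocation. Week 12 precedes the detraining treatment, so it is a valid covariate for that factor.
2. Report A-B, C-D and the training-by-detraining interaction alongside. If pooling over training arms is not acceptable, make the two within-pair contrasts primary, with a stated multiplicity correction.
3. Express any detraining percentage change from week 12 and treat it as secondary.
4. Analyse the training-phase effect separately, at week 12 adjusted for week 0. The training coefficient in the week-16 model should not be read as that effect, because week 12 lies after training treatment.

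The cost is wording. Every measurement is already scheduled, and no visit or participant is added. Percentage change from week 0 loses its equal standing with the values in seconds.
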